#### - Secondary outcomes

Secondary outcomes of this study are hs-CRP and glucose serum levels, blood lipid profile, and HOMA index [Time Frame: Baseline, 24 h and 12 weeks after treatment].

### Sample size

The primary outcome FMD was selected as the critical variable to calculate the sample size. 49 patients (98 in total) in each group are required to have an 80% chance of detecting as significant (at the two sided 5% level) a 1% difference between the two groups in the mean FMD, with assumed standard deviation of 2.6 and a planned 15% rate of missing patients on the follow up.

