**Methods/Design:**

This randomized, single-blind clinical trial will be performed at two health centers and will include two periodontal treatment strategies. After medical/periodontal screening, a baseline endothelium-dependent brachial artery flow-mediated dilatation (FMD) and other systemic surrogate markers will be obtained from all recruited subjects. Patients then will be randomized to receive either supragingival/subgingival plaque cleaning and calculus removal plus chlorhexidine (treatment group) or supragingival plaque removal only (control group). A second and third FMD will be obtained after 24 hours and 12 weeks in both treatment arms. Each group will consist of 49 patients (n = 98) and all patients will be followed-up for secondary outcomes and will be monitored through a coordinating center. The primary outcomes are FMD differences baseline, 24 hours and 3 months after treatment. The secondary outcomes are differences in C-reactive protein (hs-CRP), glucose serum levels, blood lipid profile, and HOMA index.

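### The stated 80% power does not follow from its inputs: 49 per group with SD 2.6 and 15% loss gives about 41% power for a 1-point FMD difference

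*Protocol article*

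**What the plan says.** The Sample size section of the protocol article takes FMD, the primary outcome, as the sizing variable and states a complete calculation:

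- Size and power: "49 patients (98 in total) in each group are required to have an 80% chance of detecting as significant".
- Test level: "at the two sided 5% level".
- Target: "a 1% difference between the two groups in the mean FMD".
- Variability and loss: "with assumed standard deviation of 2.6 and a planned 15% rate of missing patients on the follow up".

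The Abstract (Methods/Design) repeats 49 per group and 98 overall, and the Study design section repeats 98. So 49 is the size of each group and 98 is the total. The Statistical analysis section plans repeated measures ANOVA for FMD. No section gives a within-patient correlation, or says whether 2.6 is the SD of a single FMD value or of its change from baseline.

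**The concern.** An effect of 1 against an SD of 2.6 is a standardised difference of 0.38. Fewer than 50 patients per group is far too few to detect that with 80% power, even before any loss to follow-up. All the inputs are printed beside the result, so this is a conflict within one paragraph and not a detail left to a fuller document.

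This paragraph is the whole justification for the trial's size on its primary outcome. If true power for 1 point is near 41%, the trial is more likely than not to miss the effect it was designed to find. A reader who trusts the 80% would then take a non-significant result as fairly strong evidence that a 1-point benefit is absent.

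**Working it through.** **Inputs (all from Sample size):** two-sided alpha 0.05 (z = 1.960), power 80% (z = 0.842), difference 1, SD 2.6, loss 15%, two equal groups of 49.

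**Required size, normal approximation**

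n per group = 2 × [(1.960 + 0.842) × SD / difference]²

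- n = 2 × (2.8016 × 2.6 / 1)² = 106.1, so 107 evaluable per group.
- Allowing for loss: 107 / 0.85 = 125.9, so 126 per group, or 252 in total.
- The exact t calculation gives 107.09, so 108 evaluable per group; the difference is immaterial.

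The stated figure of 49 is not reproduced.

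**Power at the stated size (noncentral t, standardised difference 1/2.6 = 0.385)**

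| Evaluable per group | Power for 1 point | Difference detectable with 80% power |
|---|---|---|
| 49 (no loss) | 47.0% | 1.49 |
| 42 (49 × 0.85 = 41.65, rounded) | 41.4% | 1.61 |

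The normal approximation gives 47.8% and 42.2%.

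**Other readings**

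- One-sided two-sample test: 84 evaluable per group needed, 99 after loss. Power with 49 per group is 60% with no loss and 54% with 15% loss. The text says two-sided.
- 98 read as the size of each group: 77% with no loss and 70% with loss. The Abstract rules this reading out.
- Two-sided one-sample or paired formula: 54 needed, 64 after loss. The text specifies a comparison between two groups.

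None of these gives 49 per group with 80% power.

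**What would give 49**

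- SD 1.6 with the normal formula: 2 × (2.8016 × 1.6)² = 40.2, so 41; 41 / 0.85 = 48.2, so 49. By exact t the result is 42, then 50.
- SD 2.6 in a one-sided one-sample formula: 41.8, so 42; 42 × 1.15 = 48.3, so 49. This contradicts both the two-sided test and the two-group comparison.

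The article does not show which, if either, lies behind the printed figure.

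**Could the planned analysis supply the power?** Suppose 2.6 is the SD of a single FMD value and rho is the correlation between baseline and 12 weeks. The effective SD is then 2.6 × √(1 − rho²) with baseline adjustment (ANCOVA), or 2.6 × √(2(1 − rho)) for change scores. The rho values below are assumptions, because the article gives none. Power is for 1 point at 42 per group:

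| Assumed rho | ANCOVA | Change score |
|---|---|---|
| 0.3 | 45% | 31% |
| 0.5 | 52% | 41% |
| 0.6 | 59% | 50% |
| 0.7 | 68% | 61% |

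To reach 80% the effective SD must be about 1.6. That needs rho of about 0.78 with ANCOVA or about 0.81 with change scores. If 2.6 is already the SD of the change, the 41% applies to a change-score comparison as it stands.

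**The case against.** The best counter-argument is that 41% belongs to an unadjusted two-sample t-test, whereas the plan is a repeated measures ANOVA with FMD at baseline, 24 hours and 12 weeks. If 2.6 is the SD of a single measurement and baseline is used efficiently, power is higher. It passes 50% from a correlation of about 0.46 with ANCOVA, or just above 0.60 with change scores. This stands as a limit on the size of the shortfall: the statement that the trial would more likely than not miss a 1-point effect holds for the printed inputs and not for every possible analysis. It does not rescue the 80%, which needs a correlation near 0.8 that appears nowhere in the article.

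It is also fair to say that the origin of 49 cannot be known. A misprinted SD and a wrong formula are both possible, so the fit with SD 1.6 is a hint and not a diagnosis. Absolute percentage points is the natural reading of the 1% difference, since FMD is itself defined as a percentage change in diameter under Assessment of vascular function; the calculations here use that reading.

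Finally, restating the detectable difference makes the paragraph true but leaves power for 1 point where it is. That is correct, and it is a reason to print both numbers.

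**Conclusion.** The concern holds. The stated sample size, SD, difference, loss and power cannot all be true. On the printed inputs, 49 per group gives about 41% power for a 1-point difference after 15% loss and 47% with none, against 80% claimed. The size needed is about 126 per group, roughly two and a half times what is planned. The detectable difference with 80% power is about 1.6 points.

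These figures assume a two-sided two-sample comparison, a difference in absolute FMD percentage points, and 2.6 as the SD of the quantity tested. If 2.6 is a cross-sectional SD and baseline is adjusted for, the shortfall is smaller, but 80% is not reached below a correlation of about 0.78. This must be corrected, because it is the only stated basis for the trial's size.

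**What to change.** Establish which input is wrong and rewrite the Sample size paragraph, keeping 98 patients.

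- **If SD 2.6 is right for the quantity tested:** state that 49 per group (42 evaluable after 15% loss) gives 80% power for a difference of 1.6 percentage points in mean FMD, and that power for 1 point is 41%.
- **If a different SD was intended** (1.6, the SD of the change, or the residual SD after baseline adjustment): state that value, what it is the SD of and where it comes from. If it depends on a correlation between baseline and 12 weeks, state the correlation too.

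In either case, say that the difference is in absolute FMD percentage points.

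The cost is one reworded paragraph and, in the first case, a less favourable power statement; no patients are added. If the sponsor instead wishes to keep 80% power for 1 point with SD 2.6, the price is about 126 per group (252 in total), which is 154 more patients than planned.

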### Randomization, allocation concealment and blinding

Subjects will be randomized into one of two groups: 1) treatment group (one stage full-mouth disinfection), and 2) control group (conventional adult prophylaxis). Randomization will be stratified on the basis of gender (male or female), and smoking status (*current smokers*: subjects who reported regular smoking of one or more cigarettes a day for at least one year; *non-smokers*: never smoke and former smokers who had stopped smoking for at least 12 months). The sequence will be generated using a random number generator in a computer by an independent researcher not involved in the interventions or measuring the clinical variables. Random permuted blocks with a size of four patients will be selected. Sequentially numbered, opaque, sealed envelopes (SNOSE) were developed for the implementation of the random sequence.

On the treatment day, a trained nurse will open the corresponding numbered envelope at the Cañaveralejo Health Center or at the dental clinics Universidad del Valle. The patient's group allocation will be given to the periodontist to perform the corresponding intervention. Due to the nature of the interventions, it is no possible to blind study participants and periodontists for the treatment protocol. Outcome evaluators and data analysts will be blinded to the group assignment. Detailed instructions on methods to maintain the blind will be given to the researchers, health care providers and outcome evaluators. Furthermore, these instructions were reinforced in bimonthly meetings with the personal involved in the study and detailed in the operations manual.

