#### - Visit III

randomization to supragingival and subgingival plaque cleaning and calculus removal, four quadrants in one session, plus chlorhexidine (treatment group, full-mouth disinfection protocol) or supragingival plaque removal (control group, adult prophylaxis). All the interventions will be performed by two qualified periodontists at the School of Dentistry (Universidad del Valle), at Cañaveralejo Health Center or at Siloe Health Center.

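### A single published block size of four, with staff who learn every allocation, makes up to a third of assignments deducible, and the site lists leave Siloe without a stated envelope opening

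*Protocol article*

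**What the plan says.** The section on randomization, allocation concealment and blinding sets out the scheme:

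- Strata: "Randomization will be stratified on the basis of gender (male or female), and smoking status", which gives four strata. Site is not a stratification factor.
- Blocks: "Random permuted blocks with a size of four patients will be selected". No variation in size is described, and the size is public.
- Concealment: an independent researcher generates the sequence, and "Sequentially numbered, opaque, sealed envelopes (SNOSE) were developed for the implementation of the random sequence".
- Release: at the treatment visit "a trained nurse will open the corresponding numbered envelope at the Cañaveralejo Health Center or at the dental clinics Universidad del Valle", and the arm is passed to the periodontist.
- Blinding: "it is no possible to blind study participants and periodontists for the treatment protocol", but "Outcome evaluators and data analysts will be blinded to the group assignment".

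On place, Visit III gives the randomised intervention "at the School of Dentistry (Universidad del Valle), at Cañaveralejo Health Center or at Siloe Health Center", which is three locations, and Visit VI names the same three. The Settings section places treatments and tests at the university and names the two health centers, with the dental school, as sources of recruitment. The abstract says the trial runs at two health centers.

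**The concern.** Sealed envelopes conceal an assignment only while its content cannot be worked out beforehand. With a known block of four and equal arms, anyone who has seen the earlier assignments in a block can sometimes name the next one. Here the people who see them are the nurse and a small team of periodontists (two under Visit III, three under Interventions), and sex and smoking status are easy to learn. A patient expected to draw a particular arm could be postponed, or lost, before the envelope is opened. Blinded outcome assessment does not correct selection that happens before assignment.

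The second issue is internal consistency. Treatment is listed at three places and envelope opening at two, so a Siloe patient has no stated place of assignment. The text also does not show how one numbered series per stratum stays in order across locations.

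**Working it through.** **Inputs.** Block size 4 and four strata (randomization section). Equal arms of 49 (abstract, sample size section), so each block is taken as two plus two; this is an assumption that follows from the 1:1 ratio. The plan gives no predictability figure to reproduce.

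**Step 1: upper bound, observer knows all earlier allocations in the stratum.** There are six equally likely orders of AABB.

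- Certain: position 4 always; position 3 when the first two match, in 2 of 6 orders. Share = (1 + 1/3)/4 = 33.3%.
- Best guess (the arm with more places left) is correct with probability 1/2, 2/3, 2/3 and 1 at positions 1 to 4. Mean = 2.833/4 = 70.8%.
- For 98 patients split 25/25/24/24 over the strata (assumed) there are 24 full blocks and two leftover first positions: 24 × 4/3 = 32 certain, or 32/98 = 32.7%.

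**Step 2: observer sees only part of a shared series.** Suppose each allocation is visible with probability q (the share handled at the observer's own site) and the position in the block is known from the envelope number.

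- Position 3 is certain with probability q²/3 (both earlier ones seen and matching).
- Position 4 is certain with probability q³ (all three seen) plus q²(1 − q) (exactly two seen and matching: 3q²(1 − q) × 1/3), which equals q².
- Share certain = (q²/3 + q²)/4 = q²/3.

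| Share seen, q | Certain | Best guess correct (simulation) |
|---|---|---|
| 1/3 | 3.7% | 57% |
| 1/2 | 8.3% | 60% |
| 2/3 | 14.8% | 63% |
| 1 | 33.3% | 71% |

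The documents give no site shares; these values of q are assumptions.

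**Step 3: randomly varied blocks.** Simulation over the same four strata. The observer sees every earlier allocation in the stratum and knows which sizes are possible, but not their order.

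| Blocks | Certain | Best guess correct |
|---|---|---|
| 4 only | 32.6% | 70.5% |
| 4 and 6 | 5.7% | 68.4% |
| 4, 6 and 8 | 2.4% | 67.0% |

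Varying the size removes most of the certainty and little of the guessing advantage.

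**Step 4: places, side by side.**

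| Section | Place |
|---|---|
| Abstract | two health centers |
| Settings | treatment at the university; Siloe and Cañaveralejo as recruitment sources |
| Visit III and Visit VI | School of Dentistry, Cañaveralejo, Siloe |
| Randomization | envelopes opened at Cañaveralejo or the university dental clinics |

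These cannot all be right. Siloe is a treating site in two sections, only a recruitment source in one, and absent where envelopes are opened.

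**The case against.** A fixed block of four with sequentially numbered sealed envelopes, independent generation and blinded assessors is a conventional scheme, and the article states real safeguards. The recruiting periodontist takes no part in treatment or follow-up, a physician assesses eligibility, and baseline FMD is measured at Visit II before assignment at Visit III. No section gives the nurse or treating periodontists a role in eligibility. All of that stands, and it narrows the route to bias.

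Three stronger readings are tempting and not supported.

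- A reader might infer that about a third of the 98 assignments will be known to staff. That needs complete knowledge of earlier allocations in each stratum. The article does not say that anyone keeps such a tally, and a series shared across sites would hide part of it.
- A reader might infer that treating staff control the date of Visit III. No section says who schedules it. Postponement is a possible route, not a described one.
- A reader might infer that one series cannot be used in order at several places, or that dividing it destroys balance. A single custodian could keep the order, and handing out whole blocks of four would preserve order within site and balance. The article mentions an operations manual and may leave such logistics to it.

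What the objection does not remove is the fixed, published size itself and the disagreement between the named places. Whole blocks sent to each site would also let local staff see all of their own blocks, which brings back the upper bound in step 1.

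**Conclusion.** The point holds as a modest, avoidable weakness in the allocation scheme together with an inconsistency over sites. Up to 33% of assignments are certain and up to 71% guessable for a fully informed observer; about 4% to 15% are certain and 57% to 63% guessable if staff see one third to two thirds of a shared series. These figures rest on two-plus-two blocks and on assumed visibility. The remaining exposure is mainly patients postponed or lost between Visits II and III. The text does not show that concealment has failed or that the FMD comparison is biased. The site mismatch is a conflict of description to be resolved, not proof that Siloe patients are assigned out of order.

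**What to change.** 1. For patients not yet randomised, have the independent researcher generate a new list within the existing gender-by-smoking strata, using randomly varied block sizes (for example 4 and 6), and keep the sizes from treating staff. On the figures above, certain predictions fall to about 6% but best-guess success only to about 68%, so this is a partial remedy.
2. Record patient ID and stratum before each assignment is released, through the existing coordinating center if feasible. The weekly calls show that the center exists, not that it can serve every treatment day, so this needs checking.
3. Reconcile the abstract, Settings, Visit III, Visit VI and the randomization section on where treatment is given and envelopes are opened, including Siloe, and state how one ordered series per stratum is followed.

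Cost: a new list, new envelopes or a release log, and slightly more chance imbalance. An unfinished block leaves at most half its size as imbalance, so the extreme over four strata rises from 4 × 2 = 8 to 4 × 3 = 12 patients, and typical values are smaller. A separate series for each site is not recommended here: three sites by four strata is 12 cells for 98 patients, about 8 each, with more unfinished blocks.

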### Periodontal examination and subgingival samples

Calibrated dentists with experience in performing periodontal examinations will perform the evaluation of the periodontal status of recruited patients. The following clinical parameters will be evaluated:

A. Number of present teeth.

B. Gingival Margin Level (GML): distance in millimeters from the cemental-enamel junction (CEJ) to the gingival margin.

C. Probing Pocket Depth (PD): Distance in millimeters from the gingival margin to the periodontal pocket as measured with a calibrated periodontal probe.

D. Clinical Attachment Level (CAL): distance in millimeters from the CEJ to the deepest aspect of the periodontal sulcus or pocket.

E. Bleeding on Probing (BOP): the presence of BOP will be expressed as yes/no at each site. The extent of BOP will be reported as a percentage of all sites.

GML, PD, and CAL will be recorded at six sites per tooth. PD and CAL will be reported in each patient as follows:

A. Mean PD

B. Mean CAL

C. Number of sites with PD ≥ 4 and PD ≥ 5

D. Number of sites with CAL ≥ 3 and CAL ≥ 4

The six deepest pockets (>4 mm) on each patient were selected for subgingival microbial samples. The supragingival plaque will be removed with cotton gauze and a sterile curette. Subsequently, two absorbent paper points (#45) are introduced to the bottom of each pocket for a period of 20 seconds. Six points will be collected in a sterile Eppendorf tube and stored at - 70°C until analysis by Polymerase Chain Reaction (PCR). The remaining six points will be placed into vials containing transport medium VMGA-III for bacterial culturing and microbial colony identification.

### Blood samples

Venous blood samples will be withdrawn from the antecubital vein in fasting conditions (8 to 10 hours). Blood samples will be collected using three vacutainer tubes, one dry, one with EDTA and another with sodium heparin. One 1000 uL aliquote of the EDTA blood sample will be used for Complete Blood Count (CBC). All remaining samples will be centrifuged at 1500 rpm during 10 minutes to extract the plasma and serum. Plasma obtained during visits II, IV and V will be stored in Eppendorf vials at -70°C until the end of the study for the analysis of cytokines by Multiplex^®^, hs-CRP and insulin. Serum samples will be immediately analyzed for measurement of glucose and lipid profile.

### Biochemical markers

Biochemical tests will be performed in the Microbiology and Immunology Laboratory, from the Universidad del Valle (Cali, Colombia) and other private certified Clinical Laboratory.

*Plasma glucose levels*: glucose measurement will be performed using enzymatic-colorimetric techniques (Selectra, Merck).

*Lipid profile*: High-density lipoproteins cholesterol (HDL-C), total cholesterol (TC) and triglycerides will be determined by enzymatic-colorimetric techniques (Selectra, Merck). Low-density lipoproteins cholesterol (LDL-C) will be calculated using the Friedwald equation: LDL-C = TC-(HDL-C+TG/2.2).

*High sensitivity C-Reactive Protein (hs-CRP)*: the fasting plasma hs-CRP concentrations will be analyzed using a solid-phase, chemiluminescent immunometric assay (Immulite 1000, Siemens).

*Complete Blood Count (CBC)*: CBC will be performed using an automated analyzer (Advia 60, Siemens).

### Luminex multiplex assay for measurement of cardiovascular risk biomarkers

Cardiovascular risk biomarkers will be determined on plasma samples using the Luminex-200 system (Luminex Corporation). This system allows measuring up to 200 proteins simultaneously in a small sample volume (25-50 μL). MILLIPLEX™ MAP biomarker panel will be used to determine the following cardiovascular risk biomarkers: MMP-9, MPO, PAI-1 (total), sE-Selectin, sICAM-1, sVCAM-1, hs-CRP, fibrinogen, haptoglobine, amyloid A and amyloid P.

### Culture of periodontopathic and superinfecting bacteria

The samples will be analyzed using microbial culture techniques for the presence of periodontopathic bacteria according to Slots[35]. Briefly, all samples will be processed before 24 hours at room atmosphere (25°C) and immediately incubated in CO_2 _and anaerobic culture systems. Brucella blood agar medium will be incubated at 35°C in an anaerobic jar for 7 days. The TSBV medium will be incubated in 10% CO_2 _in air at 37°C for 4 days. Presumptive identification will be performed according to methods described by Slots & Reynolds and Slots et al.[36,37] to identify by colony morphology and Gram stain for *Campylobacter *spp., *Eubacterium *spp., *Fusobacterium *spp., *Capnocytophaga *spp., *Dialister pneumosintes*. Colony morphology characterized by the presence of an inner star, and catalase positive test will be used to identify *Aggregatibacter actinomycetemcomitans*. In addition, *Porphyromonas gingivalis, Prevotella intermedia/nigrescens, Tannerella forsythia, Micromonas micros *and *Eikenella corrodens *will be identified by the use of a commercial micromethod system (RapID ANA II, Remel, Norcross, GA, USA). Gram-negative enteric rods will be sub-cultured and colony purified on MacConkey and Cetrimide agar plates and identified using a standardized biochemical test (API 20E^®^, bioMerieux, Inc, Marcy l'Etoile, France). Total viable counts (TVC) will be defined as the total number of colony forming units obtained on non-selective media plates. Species found on selective media will be enumerated and presented as percentage (%) and counts × 10^5^. For the isolation of enteric bacteria, MacConkey agar will be used and incubated in aerobic atmosphere at 37°C for 24-48 hours. A Gram stain will be performed to colonies that grew on MacConkey agar medium for verification. The subgingival presence of Human Cytomegalovirus (HCMV) also will be determined at these samples using a nested PCR technique.

